## Discussion

Behavioural and psychological symptoms are an intrinsic feature of dementia that are often treated with drugs such as antipsychotics, which are potentially unsafe to use in this population. Alternative treatments for BPSD are required but there is a dearth of research in the area. We have tried to design a trial of exercise as therapy for BPSD. Designing such a trial provides challenges that drugs trials do not, such as: defining the treatment, maintaining blinding, defining clear measurable outcomes and ensuring the intervention is feasible and sustainable.

Exercise provides a promising intervention for BPSD, but further work is needed. Previous studies have reported the use of relatively complex exercise regimes including aerobic, strength, flexibility and balance training [25,26]. Most ageing individuals suffer from physical conditions such as cardio-respiratory illness, arthritis, and sensory and mobility impairments. It is important, therefore, that exercise therapy for this patient population is sensitive to this. Our study group and the independent Steering Group, which monitors and advises us, agreed that 'walking' is a feasible, sustainable and cost effective way of exercising. Walking is a simple way of exercising which enjoys all the benefits of more complex exercises but with the advantage of being sustained independently even by individuals with moderate to severe dementia and other physical conditions.

Careful consideration was taken in regards to blinding the researcher to the allocation status of the participants. The single blind design leaves us vulnerable to unmasking group allocation during the interaction between researcher and participant during visits. This everyday conversation is essential to building a rapport with participants and ensuring they feel comfortable in participating. All study personnel including researchers and therapists will repeatedly remind participants of the importance of not disclosing their group allocation. However, the risk will remain, and so we decided to include a second 'independent' researcher whom would collect our primary outcome data (NPI) at 6 and 12 weeks. The premise for this approach is that this researcher can take a less 'personal' tone and thus minimize the risk of conversation with the dyad that might un-blind group allocation. However, there remains a risk that the dyad will divulge information about the group they have been allocated to. Therefore the efficacy of blinding will be assessed at each time point, by personnel collecting data who will record which arm they believe each dyad is randomised to.

Separating the effect of psychosocial contact (from the exercise therapist) from the exercise intervention has proved to be the biggest challenge in our study. We decided to address this problem by introducing two periods during the intervention: 1-6 weeks whereby the participants in the intervention group will be trained and supported by an exercise therapist and 6-12 weeks when participants will receive absolutely no contact with the therapist. This stage will also help to assess the intervention's feasibility and sustainability in a community population. The symptoms of BPSD tend to be relatively stable over short time periods (i.e. months) so the two windows provided by this method should detect responses influenced purely because of exercise and not by any residual benefits of interaction with the therapist. Although we have tried to control for contacts between participants and the exercise therapist, we could not control for the social contact between the person with dementia and their carer. Dyadic walking may encourage not just physical activity but psychosocial support from the carer as well.

In terms of outcomes, we are using measures that are validated and widely used in research with individuals with dementia. We also gave considerable thought to the issue of measuring physical activity. Particular consideration was given to the use of equipment by the participants to record their individual activities e.g. Global Positioning System receivers and pedometers. The following issues were identified:

- Measurement accuracy and information bias (participants are likely to forget to wear their equipment or they may continue to wear equipment during non-activity time);

- Practicality and intrusion (wearing equipment for 12 weeks on daily basis can be intrusive and this may affect participation in the study and may give rise differential attrition);

- Methodological problems (introducing a self administered assessment of physical activity within the control group could constitute an intervention in its own right. There is potential for this to promote increased levels of physical activity within the control group and thus reduce the detectable effect size).

Therefore, we agreed to evaluate participants' level of physical activity through measurements of the participants' self reported Rate of Perceived Exertion (exercise group only). A proxy measure of fitness will be utilised to assess for compliance with intervention. Heart rate at rest will be assessed at the beginning, middle and end of the trial for all participants. We expect that should participants adhere to the prescribed exercise regime, their fitness will improve and ergo their heart rate at rest. We hypothesise that with such an increase in activity we may observe a reduction of BPSD. However we recognise that detecting such changes in cardiovascular health may be overambitious.

Assessing physical activity with minimum intrusion to study participants is challenging and we are relying on participants' self reports through daily dairies. Self-report is prone to information bias, especially when participants are not blinded to their group allocation. We may also encounter a significant Hawthorn effect whereby participation in the study and study hypothesis in particular may affect the behaviour of study participants. Thus, participants in the control group who believe they may benefit from regular exercise might increase their physical activity during the study period, which in turn may reduce any detectable effect due to the intervention.

Antipsychotic drugs, as discussed above, provide limited efficacy in treating BPSD as well as having established safety concerns. Exercise, on the other hand, may be effective but could also be associated with unknown risks. At present we can not discern whether the unconfirmed risk of the exercise is more substantial than the demonstrated risk of drugs. However, we have attempted to develop a design with robust risk event detection to mitigate this.

Designing the Evidem-E trial has proven to be very challenging but we have attempted to overcome the challenges without compromising scientific rigour or study feasibility. This trial is in accordance with the UK government's action plan to tackle the over-prescribing of antipsychotic drugs to people with dementia.

If this trial is successful, its findings may be applicable to a wide base of people diagnosed with dementia with minimal costs.

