## Methods/Study Design

This trial has been granted ethical approval by the Outer North East London Research Ethics Committee, REC reference number: 09/H0701/67.

We will undertake a pragmatic, randomised, controlled, single-blind, parallel-group trial. Community-dwelling individuals with a diagnosis of dementia or suspected dementia who also have a carer willing and able to be a co-participant in the exercise regime will be recruited to this evaluation.

Participants will be randomly allocated to one of two arms: the treatment arm, which includes receipt of an individually tailored regime of walking (the intervention; exercise therapy-ET) in addition to treatment as usual (TAU) or the control arm which receives treatment as usual only (see Figure 1). Treatment as usual may include home care, attendance at day care facilities, visits by health professionals, receipt of medication, respite care etc.

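### The two-window design (therapist contact in weeks 1-6, none in weeks 6-12) cannot separate the effect of exercise from carry-over of therapist contact, as the Discussion claims

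*Protocol article*

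**What the plan says.** The Discussion names the separation of therapist contact from exercise as the hardest problem in the design and offers a two-period solution. In weeks 1-6 "the participants in the intervention group will be trained and supported by an exercise therapist". The second period is "6-12 weeks when participants will receive absolutely no contact with the therapist". The Discussion also gives this second period another purpose, to assess feasibility and sustainability.

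The argument for separation follows. "The symptoms of BPSD tend to be relatively stable over short time periods", meaning months, and the conclusion drawn is that "the two windows provided by this method should detect responses influenced purely because of exercise and not by any residual benefits", where the benefits meant are those left from therapist contact.

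The next sentences add a limitation about the carer: "we could not control for the social contact between the person with dementia and their carer", and "Dyadic walking may encourage not just physical activity but psychosocial support from the carer as well".

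The comparator, under Methods/Study Design, is "the control arm which receives treatment as usual only". The text with Figure 1 describes one 1:1 randomisation after the initial interview. Under Statistical Methods, continuous outcomes at 6 and 12 weeks are compared between the randomised groups by ANCOVA with the baseline score as covariate.

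**The concern.** The Discussion claims a property that the design does not have. Only the intervention arm sees a therapist, so the arms differ in therapist contact as well as in walking. Stopping the contact at week 6 removes it from the week-12 comparison only if its effect has gone by week 12. The article does not state that assumption and gives no evidence for it.

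What is at stake is interpretation. In the Background, the authors criticise previous trials because exercise was often combined with other behavioural interventions, so that its own effect was hard to isolate. A reader of the Discussion would conclude that this trial has solved that problem for therapist contact. It has not, and a positive week-12 result could be read as evidence about walking free of therapist benefit.

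**Working it through.** The disputed sentence contains no figure, so the check is one of identifiability.

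**Inputs from the article**
- Comparator: usual care only (Methods/Study Design).
- Randomisation: once, 1:1, with none described at week 6 (text with Figure 1).
- Therapist contact: intervention arm only, weeks 1-6 (Discussion).
- Analysis: arms compared at weeks 6 and 12, adjusted for the baseline score (Statistical Methods).

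**Notation** (improvement counted as positive)
- E6, E12: effect of walking itself at weeks 6 and 12.
- C: effect of therapist contact at week 6.
- r: share of C still present at week 12.
- D6, D12: effect of carer contact and any other non-exercise difference between the arms.

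The effects are taken as additive to keep the algebra simple.

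**Step 1: week 6.** The contrast is E6 + C + D6. Therapist contact is in it by design, so the first window cannot show exercise alone.

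**Step 2: week 12.** The covariate is the baseline score, so the contrast is cumulative from randomisation: E12 + rC + D12. Only this sum is estimated. The term rC vanishes only if C = 0 or r = 0.

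**Step 3: both time points together.** There are two estimable quantities and six unknowns (E6, E12, C, r, D6, D12). Set D6 = D12 = 0 and suppose that the same difference Δ is seen at both weeks. Two explanations fit equally well:
- all exercise: E6 = E12 = Δ and C = 0;
- all contact: E6 = E12 = 0, C = Δ and r = 1.

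The contact share of the week-12 difference can therefore lie anywhere from 0 to 100%, and no sample size narrows that range.

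**Step 4: change from week 6 to week 12.** The between-arm difference in change is (E12 − E6) − (1 − r)C + (D12 − D6). With no exercise or carer effect it equals −(1 − r)C, which is −C if contact washes out completely and 0 if it persists completely. It tracks the decay of the contact effect and does not isolate exercise.

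**Step 5: the stability premise.** Separation at week 12 needs r = 0. The sentence on stability most naturally describes the usual course of symptoms. A stable usual course does not make an induced benefit disappear within six weeks, so it does not supply r = 0. It also does not fix r at any other value.

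**The case against.** The strongest reply is that the sentence is hedged, stands only in the Discussion, and carries no weight in the Methods. Statistical Methods contains no test, contrast or decision rule that relies on it. The primary objective already compares a walking programme with usual care, the trial is called pragmatic, and the second window is also described as a test of sustainability. All of this stands. It limits the point to a claim about interpretation and means that the objective need not be rewritten. It does not rescue the claim, which is affirmative and which the design cannot meet.

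Three stronger readings are tempting and are not supported:
- **Stability means that the contact effect must persist to week 12.** It does not follow. A stable usual course says nothing definite about an induced change once its cause is withdrawn. Stability merely fails to support wash-out.
- **The authors would credit a positive result to exercise alone.** The sentence is set against therapist contact, and the article goes on to disclose that carer contact is uncontrolled. Only therapist carry-over is left undisclosed.
- **The test would have an inflated false-positive rate.** If therapist contact works, the package does differ from usual care, and rejecting that null hypothesis is correct. Only the attribution would be wrong.

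One matter cannot be checked. The Interventions section describes phased withdrawal using visits and telephone calls, but the schedule is in Figure 2, which is not shown. How much contact falls late in the first six weeks is therefore unknown.

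**Conclusion.** The point holds as an error of inference. With usual care as the only comparator and a single randomisation, neither time point isolates exercise from therapist contact: week 6 includes the contact, and week 12 includes whatever remains of it. No size can be put on the contact share, because the design does not identify it. The claim would be right for therapist contact at week 12 only if the contact effect were absent or fully washed out by then, and the article gives no support for either.

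The randomised comparison remains a valid estimate of the whole package against usual care at both weeks. The sample size does not depend on the disputed sentence. The conclusion rests on the article's own description of the arms, the randomisation and the analysis, and on no assumed effect size.

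**What to change.** In the Discussion, delete the claim that the two windows detect responses due purely to exercise. In its place, state that:
- the comparisons at weeks 6 and 12 both estimate the effect of the whole package, that is, therapist-supported, carer-accompanied walking plus usual care against usual care;
- week 12 shows how durable that effect is after the therapist withdraws, in line with the sustainability purpose already given;
- the effects of therapist contact and of exercise cannot be separated, because a contact effect from weeks 1-6 may carry over.

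Keep the existing statement on carer contact and put therapist carry-over beside it as a second limitation.

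The cost is wording and a narrower causal claim. Randomisation, sample size, assessments and analysis are unchanged. To keep the claim of separation, the trial would need a different design, such as a contact-matched comparator; that is not needed for the package question.
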